### 3.2.3 Exploratory Efficacy Variables

No other efficacy variables are planned to be analysed within this SAP, for the first study publication.

## 3.3 Safety Variables

### 3.3.1 Exposure and Compliance of Study Drug

Exposure will be described as per following for the treated group:

- Number of days in study that infants have been exposed to IP
- Mean daily dose of AA mg/kg/day and DHA mg/kg/day. (They are expected to be 100 and 50 mg/kg/day, respectively at the beginning of the study. Dose adjustment were to be performed after the infant has regained its birthweight and weight gain results in an increase of 0.1 ml or more.)

Compliance will be described as percentage of number of days IP received / total number of days in study \* 100.

### 3.3.2 Adverse Events

Significant AEs are collected from birth onwards during the study, as per the table below. AEs specified event and category are available for the summaries.

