##### **A. Conventional parenteral fatty acid treatment with Clinoleic**

##### **B. Enteral supplement of AA (100mg/kg/day) and DHA (50 mg/kg/day) from birth to 40 weeks postmenstrual age in addition to conventional parenteral fatty acid treatment with Clinoleic.**

Enteral supplementation with AA:DHA will start at second enteral feeding after birth and continue once daily to postmenstrual week 40 + 0. The supplementation will be delivered prior to feeding (0.1-1ml, according to dosing scheme, Appendix A). If the infant does not tolerate any enteral feeding, the supplement will be given as long as gastric retention is administered.

The intervention group will receive a daily dose of 100 mg AA/kg/day and 50 mg DHA/kg/day (Formulaid™ 2:1 DSM). Dose adjustment will be performed after the infant has regained its birthweight and weight gain results in an increase of 0.1 ml or more (see Appendix A).

Formulaid™ is produced from a blend of algal, fungal, and high oleic sunflower oils, and contains AA and DHA (triglyceride form) in a ratio of 2:1. Approximate concentrations are 265 mg/g and 135 mg/g. The study oil will be dispensed 1ml purple syringes long time stored at -80 C. Syringes are then provided to the neonatal ward where they can be stored for up to three months in +4 - +8 °C. .

As we will have clinical record forms (CRF's) online the randomization is given in the CRF when the patient's parents have agreed to participate in the study.

Randomization will be as follows; GA  $\leq$  24 weeks +6 days, n= 84, GA 25 weeks +0 days to  $\leq$  26 weeks +6 days, n= 84 and GA 27 weeks +0 days to  $\leq$  27 weeks +6 days,

n=42 (in order to receive equal number of infants with conventional treatment and infants treated with AA:DHA supplementation in relation to morbidity outcome. In order to adjust for center variability each center (n=3) will recruit as follows; GA  $\leq$  24 weeks +6 days, n= 14 (conventional) +14 (treated), GA 25 weeks+0 days to  $\leq$  26 weeks +6 days, n= 14 (conventional) +14 (treated) and GA 27 weeks +0 days to  $\leq$  27 weeks +6 days, n=7 (conventional) +7 (treated).

The treating nurse/doctor will receive the randomization on-line. The examiners (ophthalmologists, radiologists and psychologists) will be blinded for fatty acid treatment regime. The duration of parenteral nutrition and the amount of fatty acids administered will be according to clinical routines.

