### 7.3 Informed Consent/Assent Form

Informed consent by the parents/guardians for each subject will be obtained before initiating any study procedures. Both parents/guardians will have to sign the informed consent. Informed consent should be obtained as soon as possible after birth and no later than 36 hours after birth. One copy of the signed and personally dated informed consent must be given to each parent/guardian and one signed and personally dated copy must be retained in the investigator's trial records. The “Declaration of Helsinki” recommends that consent be obtained from each potential subject or parents/guardians in biomedical research trials after the physician has explained to the individual the purpose, methods, anticipated benefits, and potential hazards of the trial and discomfort it may entail.

Potential subject's parents/guardians should also be informed of their right not to participate or to withdraw from the study at any time. If the individual is in a dependent

relationship to the physician or gives consent under duress, an independent physician should obtain the informed consent. If the individual is legally incompetent (i.e., a minor or mentally incompetent), informed consent must be obtained from the parents, legal guardians, or legal representative in accordance with the law in Sweden. See the “Declaration of Helsinki”.

If a protocol amendment substantially alters the study design or there is an increase of a potential risk to the subject:

- the informed consent form or subject information sheet must be revised and submitted to EPN for review and approval; and
- the approved revised form must be signed by parents/guardians to subject currently enrolled in the study; or
- the new form must be used to obtain consent from new parents/guardians prior to enrollment into the study.

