## 8.2 Safety Evaluations

All values obtained from safety evaluations should be recorded onto the CRF. Safety evaluations consist of the following:

- **AE reporting:** include SAEs and AEs related to the study drug shall be recorded starting from receiving informed consent until the final study examination / sampling. AE reporting is further outlined in section 9, Safety.
- **Physical examination:** A complete physical examination will be performed in all subjects at birth according to standard clinical routines.
- **Vital signs:** Heart rate, blood pressure, pO2 and breath frequency will be monitored at birth and recorded in the eCRF in VIEDOC. Followed by registration of HR and MABP in excel every second hour up to day 7 PMA. Subjects are connected with continuous surveillance of heart beat, breath frequency and pO2. An alarm will notify the personnel and if any true divergences have occurred, these will be recorded in the patient record. Children with artery catheter are always under continuous intra artery blood pressure control with alarm for any irregular episodes
- Samples of ventricular & tracheal aspirate: At postnatal day 1 gastric fluid will be taken by the insertion of a feeding tube early after birth and analysed for composition e.g.inflammatory and oxidative biomarkers and fatty acids. Tracheal aspirate will be obtained during routine endotracheal suctioning daily in infants treated on ventilator and analysed for composition e.g. inflammatory and oxidative biomarkers and fatty acid composition.
- Retinal exam: Retinal exam will be performed according to clinical screening protocol. Any deviations from normal will be described in the CRF. RetCam images shall be taken if doable at each screening examination and has at least to be taken prior to treatment of severe ROP.
- Cranial/Cerebral ultrasound will be performed in all subjects by an experienced neonatologist or a pediatric radiologist as clinical routine. Any deviations from normal will be described in the CRF.
- **Cardiac Ultrasound - PDA** will be performed in all subjects by an experienced neonatologist or a pediatric cardiologist as clinical routine prior to PDA treatment. If the baby has not been treated for PDA, ultrasound will be performed day 3 and day 7.
- The following variables will be registered in the CRF;
  1. Width of ductus: xx mm
  2. Dominating direction of the shunt through DA: left-right/equilibrium/right-left

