## **9 SAFETY**

### **9.1 Recording Adverse Events**

Adverse events related to study drug must be recorded starting from the time of informed consent until the final study examination / sampling day. Any medical condition present at the initial study day (birth day), which remains unchanged or improves, should not be recorded as an adverse event at subsequent examination / sampling days. However, if there is **deterioration** of a medical condition that was present at the initial study day (birth, day 0), this should be considered a **new** adverse event and reported. This information is collected by examining the subject. Ongoing adverse events at the final study day should be followed until the event is resolved or remains stable.

Clinically significant changes (abnormalities), in the judgment of the investigator, in physical examination from the baseline exam will be recorded as an adverse event.

The following information must be collected and recorded for each AE:

- AE term (diagnosis)
- Action taken regarding AE
- AE outcome (resolved, ongoing, death, or lost to follow-up)
- AE causality (not related, possibly related, related)

The investigator should determine study drug relationship for each adverse event. AEs occurring prior to administration of the study drug will be considered as not related to the study drug. The Investigator will be using the following explanations for assessment of causality:

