### 3.2.2 Secondary Efficacy Variables

Following secondary efficacy variables will be analysed:

- Postnatal serum fatty acid (in mol%) composition in preterm infants with and without AA:DHA supplementation (at 0h, 72h, day 7, day 14, every second week until PMA of 29 weeks and thereafter at 30, 32, 34, 36, 40 weeks PMA). Missing data will not be imputed, analysis will be performed using Mixed Models for Repeated Measures (MMRM) where missing data at random is assumed.
- Outcome of neonatal morbidities (reported as Adverse Events [AE] from birth to 40 weeks PMA)
  - BPD – this morbidity is evaluated at 36 weeks PMA and will be analysed including the complete ITT population with deaths considered as non-events but their follow-up time will contribute to the total follow-up in the analyses of event rate performed by Poisson regression. Sensitivity analysis of BPD will be performed handling all deaths as endpoint also beside confirmed BPD. Drop-out due to other reasons will be considered as non-event.
  - IVH grade 0-4 – this morbidity is evaluated at an early stage post-birth, and larger amount of missing data is not expected. Drop-outs with missing IVH will be handled as non-events. Sensitivity analysis of IVH will be performed handling all deaths with missing IVH as worst value of this endpoint (?). Drop-out due to other reasons will be considered as non-event. Analyses will be performed using Mantel-Haenszel Chi-square test.
  - PDA - this morbidity is evaluated at an early stage post-birth, and larger amount of missing data is not expected. Drop-outs with missing PDA will be handled as non-events. Sensitivity analysis of PDA will be performed handling all deaths with missing PDA as event (?). Drop-out due to other

|                                     |  |                                    |               |
|-------------------------------------|--|------------------------------------|---------------|
| STATISTISKA KONSULTGRUPPEN   |  | Statistical Analysis Plan          |               |
| Protocol:
Mega Donna Mega |  | Protocol No:
MEGADONNAMEGA 16-7 |               |
|                                     |  | Version:
1.0                    | Page 14 of 21 |

reasons will be considered as non-event. Analyses will be performed using Fisher's Exact test.

- NEC – this morbidity will be analysed in the same way as the primary variable, using Poisson regression in the main and survival analysis in the sensitivity analysis.

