#### 4.7.2 *Adverse Events*

AEs will be summarized for safety population.

A summary of subjects reporting at least one of the following AEs will be presented in an overview table:

- Any AE
- Any SAE
- Any treatment-related AE
- Any treatment-related SAE
- Any AE leading to discontinuation
- Death

Summaries per SOC and PT presenting n (%) of AEs and n (%) of subjects with at least one AE will be provided for:

- All AEs (includes all serious and non-serious AEs)
- All AEs by maximum reported intensity
- All AEs by causality
- All SAEs
- All AEs leading to discontinuation

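### The SAP counts adverse events from birth with no post-randomisation restriction, so some early all-cause safety rows can include events that precede allocation

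*Combined protocol and SAP*

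**What the plan says.** **Start of counting in the SAP.** Section 3.3.2: "Significant AEs are collected from birth onwards during the study, as per the table below". Section 3.2.2 uses the same start for the morbidities taken from AE reports: "Outcome of neonatal morbidities (reported as Adverse Events [AE] from birth to 40 weeks PMA".

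**Start of recording in the protocol.** Section 9.1: "Adverse events related to study drug must be recorded starting from the time of informed consent until the final study examination / sampling day". Section 8.2 says that AEs "shall be recorded starting from receiving informed consent until the final study examination / sampling".

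**Consent and allocation.** Protocol 7.3: "Informed consent should be obtained as soon as possible after birth and no later than 36 hours after birth". Protocol section 4: "the randomization is given in the CRF when the patient's parents have agreed to participate in the study". No separate time limit for allocation is given.

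**What is tabulated.** SAP 4.7.2 plans an overview table and summaries that include "All AEs (includes all serious and non-serious AEs", all SAEs, AEs by maximum intensity and AEs by causality. It sets no condition on onset relative to randomisation or first dose. The note that widens the safety population to all randomised infants adds no onset condition either.

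**Partial safeguards.** Protocol 9.1 does not count a condition present on the day of birth unless it gets worse, and it classes events before the first dose as unrelated to the study drug.

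SAP section 6 reports no departure from protocol version 7b.

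**The concern.** Randomisation makes the arms comparable from allocation onward. An event before allocation cannot be an effect of the supplement, so in a by-arm table it is background noise. Once an infant has been counted in a row of the type 'at least one event', a later event of the same kind no longer changes that row. Equal early background in both arms therefore pulls subject-level contrasts toward no difference, which is the unhelpful direction when the purpose is to detect harm.

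The all-cause rows matter most here. Controls receive no study drug and the treating staff know the allocation, so counts of treatment-related events do not give a fair contrast between arms. The all-cause rows carry the comparison, and they are the ones without an onset condition.

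**Working it through.** The plan gives no figure on this point to reproduce: there is no rate of early AEs and no precision or power statement for safety. The check therefore sets the passages side by side and then works through the arithmetic with assumed rates.

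**1. The gap.** SAP counting starts at birth. Protocol recording starts at consent, at most 36 hours after birth. Allocation follows parental agreement. There is thus an interval before allocation in which an event counts under SAP 3.3.2 and nothing in SAP 4.7.2 removes it.

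**2. Which rows are exposed.** From the AE classification table in SAP 3.3.2:
- Can occur in the first hours: respiratory insufficiency with intubation, pneumothorax, pulmonary haemorrhage, treated hypotension, glucose below 2.6 mmol/L. Major congenital malformation can by its nature only predate allocation.
- Graded only as severe: intubation and pneumothorax. One early event already places the infant in the top category of the maximum-intensity table.
- Essentially not exposed: ROP, chronic lung disease and untreated PDA at 7 days or more. Death is also hardly affected, because an infant must survive to consent to be randomised.

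**3. Size of the attenuation.** Let q be the share of infants with a pre-allocation event in a given row, the same in both arms. Let p be the risk of such an event after allocation, assumed independent of the early event. The tabulated risk is

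observed = q + (1 − q) × p,

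so the risk difference becomes (1 − q) × (p₁ − p₀). Neither q nor p is in the documents. All rates below are assumptions.

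Worked line, p₀ = 0.20, p₁ = 0.35, q = 0.30: control 0.30 + 0.70 × 0.20 = 0.440; supplement 0.30 + 0.70 × 0.35 = 0.545; difference 0.105 = 0.70 × 0.15; ratio 0.545 / 0.440 = 1.24.

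| q (assumed) | Control | Supplement | Risk difference (points) | Risk ratio |
|---|---|---|---|---|
| 0% | 20.0% | 35.0% | 15.0 | 1.75 |
| 10% | 28.0% | 41.5% | 13.5 | 1.48 |
| 30% | 44.0% | 54.5% | 10.5 | 1.24 |
| 50% | 60.0% | 67.5% | 7.5 | 1.13 |
| 70% | 76.0% | 80.5% | 4.5 | 1.06 |

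A second assumed pair, 10% v 20%, behaves the same way: the ratio of 2.00 becomes 1.47 (19% v 28%) at q = 10%, 1.19 (37% v 44%) at q = 30% and 1.09 (55% v 60%) at q = 50%.

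**The case against.** **Protocol 9.1 already handles part of this.** That stands in part. If the rule on conditions present on the day of birth was applied, some first-day events were never recorded. It does not clearly cover events that arise after the day of birth but before consent, and the SAP does not repeat it. The rule on pre-dose causality, with the causality tables in SAP 4.7.2, labels early events but does not take them out of the all-cause rows.

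**36 hours is an outer limit.** That stands. Consent is to be sought as early as possible, and protocol 6.2 plans the first dose within 24 hours of birth, so the interval will often be shorter. (The 24-hour plan and the 36-hour consent limit do not fit together and need reconciling.)

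**Event counts do not saturate.** That stands. SAP 4.7.2 also reports numbers of events, and an equal background does not shrink their absolute difference. The attenuation concerns subject-level rows.

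**'By arm' is an inference.** That stands. SAP 4.7.2 does not name treatment groups. The inference is reasonable, because the safety population was extended to both arms.

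Three stronger readings are tempting, and the documents do not support them:
- *Harms are diluted throughout the AE summaries.* Only early all-cause rows are exposed.
- *Sites recorded different events depending on the document they followed.* SAP version 1.0 is dated 19 November 2019, after the planned last-subject completion of September 2018, and it describes ROP assessment and the interim reviews in the past tense. It gave sites no competing instruction.
- *A known loss of power.* With 105 per arm and the assumed 20% v 35%, a two-sided 5% test would fall from power 0.69 to 0.54 at q = 10% and 0.20 at q = 50%. But the rates are invented for illustration, and SAP 4.7.2 plans n (%) summaries with no stated test.

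**Conclusion.** The inconsistency is real: the SAP starts at birth, the protocol at consent, and no onset restriction separates events before allocation from those after it. Under the stated rule, early all-cause AE and SAE rows can include events that the supplement could not have caused, and subject-level differences in those rows are attenuated by the factor (1 − q).

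The size is unknown, because q cannot be obtained from the documents. The illustration assumes that q is equal in the two arms and independent of later risk. The protocol's two safeguards reduce the problem without removing it.

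A reader might infer that the safety comparison is tilted in favour of the supplement. It is not, in expectation: randomisation balances pre-allocation events, so the effect is attenuation and noise in some descriptive rows, not a shift toward either arm.

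**What to change.** 1. Reconcile the AE start point in SAP 3.3.2 with protocol 8.2 and 9.1.
2. In SAP 4.7.2, state that AE and SAE tables are presented by randomised arm and restricted to events with onset or worsening after randomisation, with the same time zero in both arms. Randomisation is the natural choice, because controls have no first dose. Counting worsening is consistent with protocol 9.1, which treats deterioration of a day-0 condition as a new event.
3. List earlier events separately as baseline morbidity.
4. Where only an onset date is available, state one rule for events on the day of randomisation and apply it to both arms.

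The cost is SAP wording, one restriction in the programming and one extra listing. Absolute AE counts will be lower. The restriction needs onset data. Protocol 9.1 does not list onset among the required AE fields, but the planned survival analysis of NEC (SAP 3.2.2), one of the morbidities reported as AEs, implies that onset dates exist. Clock times are not assured, so some imprecision for same-day events will remain. No change to design or clinical conduct is involved.

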**Table. Classification of AEs**

| Category    | Event                      | comments             | Mild | Moderate | Severe |
|-------------|----------------------------|----------------------|------|----------|--------|
| Respiratory | Respiratory insufficiency, | requiring intubation |      |          | x      |
|             | Pulmonary haemorrhage      | with resp. symptoms  |      |          | x      |
|             | Pneumothorax               |                      |      |          | x      |
|             | Pleural effusion           |                      |      |          | x      |
|             | Apnoea                     | treated medically    | x    |          |        |

|              |                                                                   |                                                          |   |   |   |
|--------------|-------------------------------------------------------------------|----------------------------------------------------------|---|---|---|
|              | Chronic lung disease                                              |                                                          | x | x | x |
| Circulatory  | Persistent ductus arteriosus (PDA)                                | ≥ 7 days of age without treatment                        | x |   |   |
|              | Persistent ductus arteriosus (PDA)                                | treated medically
(Ibuprofen, Paracetamol, Furosemid) |   | x |   |
|              | Persistent ductus arteriosus (PDA)                                | treated surgically                                       |   |   | x |
|              | Significant symptomatic hemorrhage                                |                                                          |   |   | x |
|              | Arterial hypotension                                              | requiring treatment                                      | x | x | x |
|              | Bleeding tendency                                                 | requiring treatment
(tranexamic acid)                 | x | x |   |
|              | Circulatory arrest                                                |                                                          |   |   | x |
| Infection    | Septicemia                                                        | With severe clinical symptoms                            |   |   | x |
|              | Septicemia                                                        | with mild clinical symptoms                              |   | x |   |
|              | Suspected septicemia                                              | Blood culture negative                                   | x | x |   |
|              |                                                                   |                                                          |   |   | x |
|              | Other infection                                                   | viral, cutaneous                                         | x | x | x |
| Neurological | Subependymal hemorrhage                                           |                                                          |   | x |   |
|              | Intraventricular hemorrhage grade 2                               |                                                          |   | x | x |
|              | Intraventricular hemorrhage grade 3 and/or parenchymal hemorrhage |                                                          |   |   | x |
|              | Periventricular leukomalacia                                      | cystic lesions as defined by ultrasound/MR               |   |   | x |
|              | Periventricular echodensities                                     |                                                          |   | x |   |
|              | Posthemorrhagic hydrocephalus                                     | requiring treatment                                      |   |   | x |

|                                     |  |                                    |               |
|-------------------------------------|--|------------------------------------|---------------|
| STATISTISKA KONSULTGRUPPEN   |  | Statistical Analysis Plan          |               |
| Protocol:
Mega Donna Mega |  | Protocol No:
MEGADONNAMEGA 16-7 |               |
|                                     |  | Version:
1.0                    | Page 16 of 21 |

|                     |                               |                                          |   |   |   |
|---------------------|-------------------------------|------------------------------------------|---|---|---|
| Gastro - intestinal | Necrotizing enterocolitis     |                                          |   |   | x |
|                     | Bowel perforation             |                                          |   |   | x |
| Metabolic           | Hyperglycemia                 | fasting p-gl >10mmol/L in 2 samplings    |   | x |   |
|                     | Hypoglycemia                  | <2,6 mmol/L                              |   | x |   |
|                     | Hyperbilirubinemia            | Requiring phototherapy                   | x |   |   |
| ROP                 | Retinopathy Of Prematurity    | Stage 1, 2                               | x |   |   |
|                     | Retinopathy Of Prematurity    | Stage 3                                  |   | x |   |
|                     | Retinopathy Of Prematurity    | Laser/anti-VEGF treatment and stage 4, 5 |   |   | x |
| Other               | Major congenital malformation |                                          |   |   | x |

